### Study measurements

Demographic and baseline data will be extracted from the medical record. This includes sex, age, performance status, comorbidities, treatment with systemic and/or radiotherapy during the study period and the type and dose (converted to morphine equivalents) of the opioid which the patient will use.

The primary outcome measure is the proportion of patients with a score of < 30 on the Bowel Function Index (BFI), measured on day 14. The BFI is a clinician-administered, patient-reported questionnaire to assess clinically significant constipation, validated in patients receiving opioids for chronic non-malignant and malignant pain [20–22]. The BFI consists of three questions, assessing ease of defecation, feeling of incomplete bowel evacuation and personal judgement of the patient regarding constipation, each during the last 7 days and each rated on a scale of 0 (best possible outcome) to 100 (worst possible outcome). A total score ≥ 30 (mean of the three separate scores) indicates clinically significant constipation. A change of the total score of > 12 is regarded as clinically meaningful. The BFI has been used in a large ‘real world’ observational study in cancer patients receiving opioids [1] and in randomized trials of opioid antagonists for OIC [23–26]. It has been recommended as the assessment tool of choice for OIC [7, 27]. The BFI will be administered by the local investigator on day 0 (at the start of the study, after giving informed consent and before the randomization) and by telephone on day 14.

As a secondary outcome measure, the local investigator will assess the Rome IV criteria for opioid-induced constipation on day 0 and by telephone on day 14 (see Table 1). At least two of the six criteria have to be fulfilled in order to diagnose constipation.

Another secondary outcome measure is the 5-level EuroQol-5 Dimension questionnaire (EQ-5D-5L) completed on day 0 and 14. The EQ-5D-5L is a self-administered, generic assessment tool developed by the EuroQol Group to assess the quality of life and to determine cost-effectiveness. This measurement tool consists of five questions on dimensions of health (i.e., mobility, self-care, pain/discomfort, usual activities, and anxiety/depression) [28].

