Other secondary outcome measures include a pain score (Numeric Rating Scale, ranging from 0 to 10, on days 0 and 14), a questionnaire about patient satisfaction with the laxative on day 14 (one question on a four-point Likert scale, ranging from unsatisfied to very satisfied), a questionnaire about side effects of the laxatives on day 14 and a questionnaire about medical consumption (the modified iMTA Medical Consumption Questionnaire (iMCQ)) on day 14 [29]. An overview of the measurement tools can be found in Table 1.

Lastly, patients will report daily laxative use in a medication diary to evaluate protocol adherence and also daily use of escape medication.

**Table 1 Tab1:** Overview of measurement tools

Measurement tool	
Bowel Function Index (Day 0 and day 14)	3 questions about defecation, rated on a scale of 0 (best possible outcome) to 100 (worst possible outcome). Total score ≥ 30 (mean of the three separate scores) indicates clinically significant constipation. A change of the total score of > 12 is regarded as clinically meaningful.
Rome IV criteria for opioid-induced constipation (Day 0 and day 14)	At least two of the following criteria have to be fulfilled in order to diagnose constipation: - Straining > 25% of defecations - Lumpy or hard stools in > 25% of defecations - Sensation of incomplete evacuation in > 25% of defecations - Sensation of anorectal obstruction/blockage in > 25% of defecations - Manual manoeuvres to facilitate > 25% of defecations - < 3 spontaneous defecations per week
EQ-5D-5L questionnaire (Day 0 and day 14)	5 questions on dimension of health: mobility, self-care, pain/discomfort, usual activities, and anxiety/depression. Each dimension consists of 5 levels: no problems, slight problems, moderate problems, severe problems and extreme problems
Pain (Day 0 and day 14)	Numeric rating scale (0 = no pain, 10 = worst pain imaginable) Satisfaction with laxatives will be scored on a four-point Likert scale, ranging from unsatisfied to very satisfied Side effects of laxatives (i.e. bad taste, flatulence and nausea) will be scored on a four-point Likert scale (not at all, a bit, rather, very much)
Patient satisfaction (Day 14)	
Side effects (Day 14)	
Modified iMCQ (Day 14)	9 questions related to frequent occurring contact with healthcare providers. Each answer is dichotomous (yes/no) with the option to add the number of visits if the answer ‘yes’ is filled in.

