Secondary analyses include the same analyses for constipation judged by professional care givers, based on the Rome IV criteria for opioid-induced constipation. Furthermore, we aim to study baseline predictors of the response to macrogol/electrolytes and magnesium hydroxide in patients starting with opioids, including sex, age, performance status and comorbidity.

Lastly, the cost-effectiveness of macrogol/electrolyte compared to magnesium hydroxide will also be a secondary outcome. The cost-effectiveness will primarily be influenced by the effect of the medication on healthcare resource use and quality of life, since their unit costs are similar. In this analysis, we will compare the cost-effectiveness of macrogol/electrolyte and magnesium hydroxide in patients. The analysis will be performed from a healthcare perspective with a time horizon of two weeks. A decision tree will be developed with branches for initial therapy and responders and non-responders. The costs and quality of life of the patients in the trial will be used as input for this decision tree. This requires data collection on healthcare procedures and quality of life in responders, non-responders and patients with side-effects of laxatives for the follow-up period of the study (two weeks). These healthcare procedures will be extracted from the modified iMCQ after two weeks. The modified iMCQ will be adjusted in such a way that resource use due to gastrointestinal complaints will only be measured in these patients with intensive healthcare resource use. All individual health care procedures will be linked to their unit costs. Reimbursement prices issued by the Dutch Healthcare Authority (NZa) and national reference prices will be used for this assessment as outlined in current Dutch pharmaco-economic guidance. Quality of life will be measured using the EQ-5D-5L at baseline and after two weeks.

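### Nausea and flatulence are scored only on day 14, so symptoms already present cannot be separated from new ones and the side-effect comparison is less precise than it could be

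*Protocol article*

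**What the plan says.** In the protocol article, Study measurements, the side-effect assessment is "a questionnaire about side effects of the laxatives on day 14". Table 1 agrees on day 14 and describes the items: "Side effects of laxatives (i.e. bad taste, flatulence and nausea) will be scored on a four-point Likert scale". The four grades express severity. No step that asks whether the laxative caused the symptom is described.

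The other patient-reported symptom measures (BFI, Rome IV criteria, EQ-5D-5L and the pain score) are taken on day 0 and again on day 14. The data extracted from the medical record are introduced by "This includes sex, age, performance status, comorbidities, treatment with systemic and/or radiotherapy during the study period", followed by opioid type and dose. A nausea or flatulence score is not among them, and the five EQ-5D-5L dimensions do not cover these symptoms separately.

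The Abstract and the Background both name the comparison of side effects and tolerability as an aim. Under Statistical analysis, the economic evaluation needs data on healthcare procedures and "quality of life in responders, non-responders and patients with side-effects of laxatives".

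**The concern.** Nausea and flatulence are not specific to laxatives. The patients have incurable cancer and are starting slow-release or transdermal opioids. The protocol also expects some to have "treatment with systemic and/or radiotherapy during the study period". Some will have nausea or flatulence before they take any study laxative. With a day-14 score alone, those patients look the same as patients whose symptom is new.

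Two things are at stake, both secondary. The between-arm comparison carries variation that a baseline score could have removed. And the day-14 frequency in each arm will be reported under the label of laxative side effects, although part of it was there before. The visit schedule fixes this: no analysis plan can recover a day-0 score that was not collected.

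**Working it through.** **1. The plan's own figure.** The document gives no calculation for side effects, so the available sample size is that of the primary comparison. From Sample size calculation: 82% responders in both arms, margin 15 points, one-sided 2.5%, power 90%.

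n per arm = (1.960 + 1.282)² × 2 × 0.82 × 0.18 / 0.15² = 10.51 × 0.2952 / 0.0225 ≈ 138. This matches the stated 138 evaluable patients per arm, which is used below.

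**2. Is the between-arm difference biased?** Write b for the probability of a symptom from other causes and q for the probability that the laxative causes it. The observed rate is p = 1 − (1 − b)(1 − q). Randomization makes b equal in expectation in the two arms. If q is also equal, the expected difference is 0. The missing baseline therefore introduces no bias.

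**3. Can the per-arm rate be read as laxative-caused?** No. As an illustration, assume q = 10% in one arm and 20% in the other:

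| Background b | Observed rates | Difference |
|---|---|---|
| 0 | 10% vs 20% | 10 points |
| 20% | 28% vs 36% | 8 points |
| 40% | 46% vs 52% | 6 points |

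The rates rise with the background and the difference shrinks. With 138 per arm and a two-sided 5% test, power is 64%, 30% and 17%. A day-0 score would win back only part of this, because b also includes symptoms that start after day 0.

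**4. What would a day-0 score gain?** With the baseline as covariate, the variance of the arm difference is multiplied by 1 − ρ², where ρ is the correlation between the day-0 and day-14 scores. The documents give no ρ, so a range is assumed.

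| ρ | Variance removed | Equivalent n per arm | 95% CI half-width (SD units) |
|---|---|---|---|
| no baseline | 0 | 138 | 1.96 × √(2/138) = 0.236 |
| 0.3 | 9% | 138/0.91 = 152 | 0.225 |
| 0.5 | 25% | 138/0.75 = 184 | 0.204 |
| 0.6 | 36% | 138/0.64 = 216 | 0.236 × 0.8 = 0.189 |

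**5. Check on a four-level score.** A coarse scale weakens the observed correlation. A normal latent symptom was cut at 0.5, 1.2 and 1.9 SD into four grades, with 138 per arm and 4,000 simulated trials, with no arm effect and with a latent shift of 0.3 SD. Variance removed by adjustment:

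- latent correlation 0.3: about 4% (ratios 0.959 and 0.963)
- latent correlation 0.5: 15-16% (ratios 0.851 and 0.839)

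The mean arm difference was the same with and without adjustment (for example 0.2046 and 0.2050 at correlation 0.5 with the shift). This agrees with step 2: the gain is in precision.

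**The case against.** The text and Table 1 agree with each other, the outcome is secondary and unpowered, and keeping the questionnaire burden low is an explicit design aim in the Discussion. All of that is correct. The choice is defensible and the point is only that it can be improved. Two Likert items add little to the baseline questionnaires already in place.

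The questionnaire wording is not shown. If it asks what the laxative caused, a day-0 version in the same words would make no sense, because laxative use in the previous four weeks is an exclusion criterion. Patients would then do some of the attribution themselves, and misattribution would be smaller, though not gone. This stands, and it is why the day-0 items must be worded as symptoms. The list of baseline data may also be condensed in an article, but Table 1 states the side-effect timing plainly.

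Three stronger readings are tempting and not supported:

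- *That most patients recorded with a side effect did not get it from the laxative.* The share is b/(b + (1 − b)q). Assuming b = 10% and q = 10% gives 0.10/0.19 = 53%, and b = 30% with q = 5% gives 0.30/0.335 = 90%. But b = 10% with q = 20% gives 0.10/0.28 = 36%. The documents supply neither input, and b here includes symptoms that begin after day 0, which no baseline could identify.
- *That a day-0 score would separate out the effects of the opioid and of anticancer treatment.* Opioid and laxative start at about the same time. Hospitalized patients are asked for consent within 24 hours after the opioid starts, so day 0 may catch some early opioid nausea. Later nausea would still count as new.
- *That the economic evaluation is corrupted.* The Statistical analysis section mentions patients with side effects as a group for data collection, but the named branches of the decision tree are initial therapy and response status. It does not say that the day-14 score defines the side-effect group.

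**Conclusion.** The point holds as a low-cost improvement. The side-effect items have no day-0 score, so existing nausea and flatulence cannot be told from new symptoms. The missing baseline does not bias the comparison between arms, and the primary non-inferiority analysis and its sample size are unaffected.

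The loss is one of precision and of interpretation. On assumed correlations, adjustment would remove 9-36% of the variance (ρ 0.3-0.6), or about 4-16% for a four-level score at latent correlations of 0.3-0.5. At the low end this is small. The per-arm rates cannot be read as laxative-caused, with or without a baseline. A day-0 score narrows that gap for symptoms already present and no further.

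**What to change.** - Ask the nausea and flatulence items on day 0 with the other baseline questionnaires, before randomization, on the same four-point scale and worded as symptoms. Use the same symptom wording on day 14. Bad taste of the laxative needs no baseline.
- Compare the day-14 scores between arms with adjustment for the day-0 score.
- Also report symptoms that are new or worsened since day 0, and use that definition for any side-effect group in the cost-effectiveness analysis.
- State in the report that symptoms from the opioid or anticancer treatment that begin after day 0 remain mixed in, so that only the between-arm difference, not the rate in each arm, can be attributed to the laxative.

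The cost is a small amendment to the day-0 form and two extra items per patient. Patients already enrolled will have no baseline. They can stay in the between-arm comparison with an indicator for the missing score, since whether it was collected depends on the enrolment date and not on the arm. If recruitment has ended, only the last item remains possible, and the results should then be presented as day-14 symptoms.

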At present, naldemedine is not yet globally available [11] and costs on average 376,74 dollars (348,19 euros) for a 30-day supply [12], making it is less accessible compared to traditional and widely available laxatives such as macrogol/electrolytes or magnesium hydroxide with a cost of around 5 euros (5,40 dollars) for a 30-day supply [13, 14].

Despite the lack of evidence from other randomized controlled trials on the prevention of OIC by the more traditional laxatives, Dutch and other national guidelines on constipation in cancer patients recommend either macrogol/electrolytes or magnesium compounds (including magnesium hydroxide) as first-line laxative treatment to prevent OIC [15–17].

To gain evidence for these guideline recommendations, the OMAMA study examines if magnesium hydroxide is non-inferior to macrogol/electrolytes in the prevention of OIC in patients with metastatic or locally advanced incurable cancer and compares side-effects, tolerability and cost-effectiveness.

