### Statistical analysis

All data will be coded and collected in a secure cloud-based clinical data management platform (Castor EDC). Analysis will be performed using the latest version of IBM SPSS Statistics.

Primary analysis for non-inferiority will be performed both on a protocol and intention-to-treat basis. The primary outcome is the difference in proportion of responders (BFI < 30 at day 14) between the two arms. The primary analysis will use the Newcombe score method to estimate a one-sided 97.5% confidence interval for the difference in proportion of responders (proportion responders under magnesium hydroxide minus proportion responder under macrogol/electrolytes). The null hypothesis (H0: Magnesium hydroxide is inferior to macrogol/electrolytes in the prevention of OIC) will be rejected and non-inferiority will be claimed for magnesium hydroxide if the lower boundary of the 97.5% confidence interval is larger than the prespecified non-inferiority margin of -15%. An additional analysis will be performed in which the risk difference for response is estimated using a generalized linear model for a binomial outcome and an identity link, while adjusting for the stratification factors of center and constipation at the start of the study.

An additional per protocol analysis will be performed using inverse-probability-of-treatment-weighing (IPTW) in the intention-to-treat population. For this IPTW analysis, logistic regression analysis in the intention-to-treat population will be used to predict the probability of a subject being adherent based on predefined confounders. In this analysis, non-adherence is defined as < 80% of the prescribed laxative being taken as determined from the patient diary [35]. The inverse of the predicted probabilities will then be used as weights in an analysis comparing treatment outcomes between the groups and to estimate a per-protocol effect. In this weighted analysis, the risk difference for response and its two sided 95% confidence interval is estimated using generalized linear models for a binomial outcome and an identity link, while adjusting for the stratification factors.

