## Conclusion

The OMAMA study will evaluate if magnesium hydroxide is non-inferior to macrogol/electrolytes in the prevention of opioid-induced constipation in patients with metastatic or locally advanced incurable cancer. Both laxatives are commonly used as a preventive medicine, yet scientific evidence is scarce. Our study will provide evidence on the prevention of OIC and will compare the tolerability and side-effects of both laxatives. The OMAMA study has started recruitment in October 2022 and is expected to be completed in 2 years.

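### The side-effect list in Table 1 omits diarrhoea and abdominal cramps, and no other described outcome records them directly, so the tolerability comparison misses the direct effect of over-treatment

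*Protocol article*

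**What the plan says.** The Background says that the study "compares side-effects, tolerability and cost-effectiveness" alongside its non-inferiority question. The Conclusion repeats that it "will compare the tolerability and side-effects of both laxatives". The Abstract gives the same aim.

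Under Study measurements, the instrument for this aim is "a questionnaire about side effects of the laxatives on day 14". Table 1 gives its content: "Side effects of laxatives (i.e. bad taste, flatulence and nausea) will be scored on a four-point Likert scale".

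The two constipation measures are the Bowel Function Index (BFI) and the Rome IV criteria. The BFI has three items, "assessing ease of defecation, feeling of incomplete bowel evacuation and personal judgement of the patient regarding constipation", "each rated on a scale of 0 (best possible outcome) to 100 (worst possible outcome"). In the Statistical analysis section, "The primary outcome is the difference in proportion of responders (BFI < 30 at day 14) between the two arms". The only stool-form criterion in the Rome IV list is "Lumpy or hard stools in > 25% of defecations".

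The section on cost-effectiveness, within Statistical analysis, asks for care and quality-of-life data in three groups: responders, non-responders and patients who have laxative side effects.

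**The concern.** A laxative can fail in two directions: too little effect or too much. The efficacy outcomes look only at the first. The second should therefore be picked up by the side-effect questionnaire, but its three items do not include loose stools or cramps. According to the Treatment section, either dose may be doubled during the study (1 to 2 sachets; 724 to 1448 mg three times a day), so over-treatment is a foreseeable event in both arms.

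Two things are at stake. First, the laxatives could look alike on BFI response and on taste, flatulence and nausea, yet differ clearly in how often they cause diarrhoea. The report could not show this from a planned outcome. Second, the decision tree needs to identify patients with side effects. The questionnaire would not identify a patient who has diarrhoea but none of the three listed complaints.

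**Working it through.** **The plan's own figure.** Inputs from Sample size calculation and Statistical analysis: 82% response in both arms, margin 15 points, one-sided 2.5%, power 90%.

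n per arm = (1.960 + 1.282)² × 2 × 0.82 × 0.18 / 0.15² = 10.507 × 0.2952 / 0.0225 = 137.9, rounded up to 138. This matches the stated 138. Adding 20% gives 138 × 1.2 = 165.6, in line with the stated 165. None of these inputs concerns side effects, so the point leaves the sample size as it is.

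**Is the list closed?** The article introduces it with i.e. It uses i.e. elsewhere for complete sets: the five EQ-5D-5L dimensions under Study measurements and the definition of the patient group in the Discussion. It uses e.g. for an open list, the magnesium compounds in the Background. On the article's own usage, the three items are the whole list.

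**Does another outcome fill the gap?**

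| Outcome | What it asks | Loose stools or cramps recorded directly? |
|---|---|---|
| BFI | three constipation items, 0 is best | no |
| Rome IV | straining, hard stools, incomplete evacuation, blockage, manual help, fewer than 3 defecations a week | no |
| EQ-5D-5L | five general dimensions, one of them pain/discomfort | no, not specific |
| Satisfaction | one question | no, cause not asked |
| Diary | laxative and escape-medication use | no |
| Modified iMCQ | contacts with care providers; use due to gastrointestinal complaints only in heavy users of care | no |
| Dose decrease or stop (Treatment) | prompted by intolerance or side effects | no outcome described that names the cause |

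**How the responder rule treats loose stools.** The BFI score is the mean of three items. With ease of defecation and judged constipation both at 0, the score is x/3, where x is incomplete evacuation. At x = 89 the mean is 29.7, a responder; at x = 90 it is 30.0, a non-responder. A patient with loose stools who reports easy defecation and no constipation is a responder unless incomplete evacuation is scored 90 or more. The BFI does not reward looseness; it does not ask about it.

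**Illustration of what could be missed.** Assumptions not in the documents: the planned 82% response is seen in both arms, and loose stools occur in 5% of responders on one laxative and in a share d on the other. No direction between the two drugs is implied.

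Difference in response without loose stools = 0.82 × (d − 0.05):

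- d = 10%: 0.82 × 0.05 = 4.1 points
- d = 15%: 0.82 × 0.10 = 8.2 points
- d = 20%: 0.82 × 0.15 = 12.3 points
- d = 25%: 0.82 × 0.20 = 16.4 points

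In every row the primary difference is 0.82 − 0.82 = 0.

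**The case against.** **The stronger reading.** A reader might infer that the primary outcome itself is flawed because diarrhoea counts as success and could carry a drug over the non-inferiority margin. The documents do not support this. The trial asks about prevention of constipation, and the article describes the BFI as validated for that purpose in patients on opioids. A patient with loose stools and no constipation is correctly counted as not constipated. An excess of diarrhoea also does not pass one-for-one into the primary difference. Suppose an assumed excess of 10 points fell on patients with the planned 82% chance of response anyway. Only 18% of them would change status: 10 × 0.18 = 1.8 points, and even those patients are truly free of constipation.

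**Indirect signals exist.** It would also be too strong to call over-treatment invisible or the tolerability aim impossible to meet. Dose reductions and stops, the day-7 telephone contact, the diary, satisfaction, the discomfort dimension of the EQ-5D-5L and care use all bear on tolerability. That stands. What they lack is the cause: a stop for diarrhoea and a stop for bad taste look the same.

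**The article is condensed.** The questionnaire is not shown, and adverse-event recording may sit in the full protocol, so its absence here is no finding. This limits the point but does not remove it. Table 1 does not leave the content of the side-effect questionnaire open; it states a list, and the list does not serve the stated aim. If the real questionnaire is longer, Table 1 is wrong and needs correcting.

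**Conclusion.** The point holds as a gap in the tolerability outcome. As listed, the trial asks about bad taste, flatulence and nausea, and no described outcome directly records diarrhoea, loose stools or abdominal cramps. The comparison of side effects would be incomplete, and the group with laxative side effects in the cost-effectiveness analysis would be incompletely identified.

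The primary non-inferiority test, its margin and the 138 evaluable patients per arm are untouched. The documents give no rate of loose stools for either drug, so the range of 4.1 to 16.4 points only shows what could go unrecorded. It is not an expected difference.

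The conclusion rests on reading the list as closed, which the article's own usage supports, and on the general clinical premise that loose stools and cramps are the direct effects of too much laxative. It is an inexpensive improvement to a stated secondary comparison.

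**What to change.** Add two items to the day-14 side-effect questionnaire, on the existing four-point scale: diarrhoea or loose stools, and abdominal cramps. If the full questionnaire already has them, correct the list in Table 1 instead. Report both items by arm beside the primary result. A cross-tabulation of BFI < 30 by reported diarrhoea may be added as descriptive support; no new composite endpoint or cut-off is needed.

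The cost is a minor amendment and two more questions per patient. Recruitment started in October 2022 and was expected to take 2 years, so patients who have already completed day 14 will lack the items. Count them as not asked, not as free of symptoms, and state the denominator. If the items start on the same date in both arms at each centre, the comparison among patients who were asked remains a randomised one.
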